### Data analysis

The data from the interviews will be transcribed and analysed thematically to determine context and process characteristics of each organisation. Qualitative content analysis will identify underlying themes and issues, which will be used to further refine and inform the questionnaire design.

Questionnaire analysis will account for the complex interaction of multi-factorial variables and the wide range of theoretical perspectives requiring evaluation with an appropriate range of methodological tools and approaches. Given the complexity of the study and the array of variables impacting on vocal strain, there is a need to employ sophisticated forms of analysis, with the capacity to explore potential directional effects across a wide range of variables. While multiple regression analysis is frequently used to analyse social science data, the main problem is handling measurement error, indirect or mediating effects. Since most multivariate procedures cannot deal with multiple variables, particularly multiple dependent or criterion variables, hypothesis testing is difficult.

Therefore, the study will adopt a multivariate analysis approach using Structural Equation Modelling (SEM), to develop voice measurement models in determining the construct validity of potential factors contributing to Occupational Dysphonia [16]. The research design and associated analysis will therefore attempt to overcome the traditional complications of multiple indicators, indirect effects and measurement error by using structural equation modelling with latent variables and LISREL (Linear Structural Relations) estimation. SEM is a statistical methodology that takes a confirmatory (ie hypotheses-testing) approach to the multivariate analysis of a structural theory bearing on some phenomenon, representing causal processes, which generate assumptions on multiple variables [15]. The hypotheses are: 1. Call-agents' physiological voice production is improved with good vocal-working environment; 2. Call-agents' acoustic voice production is improved with good vocal-working environment; 3. Call-agents' psychosocial health is improved with good vocal-working environment. The relationships and effects of these aetiological indicators on the 'risk' of occupational dysphonia will be explored in order to determine the relative significance of physiological, behavioural environmental and psychological indicators at varying levels of severity.

Acoustic analysis will be conducted on a random sample of the voice of call-agents from call-samples using the Multi Dimensional Voice Program (MDVP), which is a software programme that provides a robust multi-dimensional analysis of voice with graphic and numerical presentation of analysis [17]. MDVP is the gold standard measurement tool for quantitative analysis of voice. From the telephone call-samples, three sections each consisting of three seconds of the call-agent's continuous voice uninterrupted by the customer will be selected during 10 seconds at the first, middle and the end of the call. Three seconds of recording is within the recommended range for acoustic analysis by the manufacturer of the voice analysis software [17]. Therefore three sections (start, middle and end) of each call-sample will be used for acoustic analysis. The voices of the call-agents in these sample-calls will be analysed for the following 14 acoustic parameters: Mean Fundamental Frequency (MFo); Highest Fundamental Frequency (Fhi); Lowest Fundamental Frequency (Flo); Standard Deviation of Fo (STD); Amplitude Tremor Frequency (Fatr); Absolute Jitter (Jita); Jitter Percent (Jitt); Shimmer in dB (ShdB); Shimmer Percent (Shim); Peak-to-Peak Amplitude Variation (vAm); Noise to Harmonic Ratio (NHR); Degree of Voice Breaks (DVB); Degree of Sub-harmonics (DSH); and Degree of Voiceless (DUV). In addition, the acoustic results will be integrated into the voice measurement model using SEM.

All numerical data will be analysed using SPSS version 15. Descriptive statistics will include means, standard deviations and ranges for each variable from the online survey and acoustic analysis. Inferential statistics such as Pearson Correlations will be used to compare the objective and subjective measures. If the assumptions for the above parametric tests are violated then the appropriate non-parametric tests such as the Mann-Whitney will be used.

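### Hypotheses 1 to 3 claim improvement from a good working environment, but single-time-point data can show only association, and for H1 and H3 exposure and outcome share one self-report questionnaire

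*Protocol article*

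**What the plan says.** The Data analysis section of the protocol article lists three hypotheses:

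- H1: "Call-agents' physiological voice production is improved with good vocal-working environment"
- H2: call-agents' "acoustic voice production is improved with good vocal-working environment"
- H3: "Call-agents' psychosocial health is improved with good vocal-working environment"

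The same section asks for an analysis "with the capacity to explore potential directional effects across a wide range of variables". It describes SEM as a hypothesis-testing method, "representing causal processes, which generate assumptions on multiple variables". It then announces that "The relationships and effects of these aetiological indicators" on occupational dysphonia will be explored.

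The data behind these statements are described elsewhere in the article. Research design and Research procedures give three stages: manager interviews, one online questionnaire, and acoustic measurement from a recorded call for a random subsample. Under Research procedures, the questionnaire is the instrument for studying the work environment. Under Main measurement tool, the same questionnaire carries the three voice scales. Participants sets at least 500 survey respondents and leaves a randomised comparison to a follow-up trial.

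**The concern.** To say that an outcome is improved by an environment is to describe a change, or at least a directed effect. Neither can be observed when each agent contributes one set of answers and no environment is altered. An agent with a strained voice may rate the room as noisier and drier, just as a noisy, dry room may strain the voice. A single wave of data does not separate the two.

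For H1 and H3 there is a second problem. One person rates both the environment and the symptoms on one form. A general tendency to complain, or not to, moves both scores together and looks like an environmental effect.

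The Abstract says that the results will inform training and workplace health policy, and Participants says that they will feed the power calculation of the follow-up trial. If the hypotheses are confirmed in the terms in which they are written, an association would be carried into both uses as a benefit of the environment, and an inflated association would make the later trial look easier to power than it is.

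**Working it through.** The article gives no power, alpha or effect size for these hypotheses, so there is no figure to reproduce. The check has three parts.

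**1. What each hypothesis needs, and what is collected**

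| Hypothesis | Environment data | Outcome data | Same source? | Repeat measure or changed environment? |
|---|---|---|---|---|
| H1 physiological | Online questionnaire | Online questionnaire (self-reported symptoms) | Yes | None described |
| H2 acoustic | Online questionnaire | MDVP analysis of a recorded call | No | None described |
| H3 psychosocial | Online questionnaire | Online questionnaire | Yes | None described |

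The article does not use the word cross-sectional; that is inferred from the stages it lists. The start, middle and end sections for acoustic analysis come from the same call, so they give no contrast between environments.

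**2. Whether model fit can supply direction**

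In the simplest case, one exposure X and one outcome Y, the Gaussian likelihood of X→Y depends on the data through var(X) × residual var(Y given X):

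s_x² × (s_y² − s_xy²/s_x²) = s_x² s_y² − s_xy²

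This is symmetric in X and Y, so Y→X gives the same value. On one simulated data set of n=500 the log-likelihood was −1376.197 in both directions. This covers the two-variable case only.

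**3. Size of the same-source problem for H1 and H3**

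Inputs: n=500 (Participants, the stated minimum); two-sided alpha 0.05 (assumed); true association zero (assumed); share m of each score's variance due to a common reporting tendency, 5% to 30% (assumed; the article gives no figure).

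Expected correlation: r = √m × √m = m.

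Probability of a significant result: Φ(atanh(r) × √(n − 3) − 1.96), with √497 = 22.29.

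| m | r | atanh(r) × 22.29 | minus 1.96 | Probability |
|---|---|---|---|---|
| 0.05 | 0.05 | 1.12 | −0.84 | 0.20 |
| 0.10 | 0.10 | 2.24 | 0.28 | 0.61 |
| 0.20 | 0.20 | 4.52 | 2.56 | 0.995 |
| 0.30 | 0.30 | 6.90 | 4.94 | about 1.00 |

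At m = 0.20 the expected test statistic is t = 0.20 × √(498/0.96) = 4.56. These are bivariate correlations, not estimates from the planned latent-variable model.

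**The case against.** The strongest reply is that the article is more cautious than the hypotheses sound. It speaks of potential factors and potential directional effects, says that its SEM is meant to develop measurement models and examine construct validity, and leaves the randomised comparison to a later trial. The phrase about causal processes is a general description of SEM. The article also condenses a fuller protocol, where limits on direction and common-method variance may be set out. All of this is fair, and it means that nobody can say how the results will in fact be reported. It does not repair the three hypotheses, which are the only formal ones and carry no hedge.

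It is also true that the 5% to 30% range is assumed and that the result depends on it: at 5% the chance of a spurious finding is 0.20, not near certainty.

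Several stronger readings are tempting, but the article does not support them:

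- **No physiological data are collected.** Main measurement tool says that the VoiSS covers physiological aspects and that items of the Vocology Screening Profile relate to physiological symptoms. What is missing is an instrumental measure.
- **The same-source problem reaches H2.** Its outcome is MDVP output from recorded speech, so only the objection to improvement and direction applies.
- **The study claims to estimate risk.** The article puts that word in quotation marks and says only that it will be explored.
- **Any reversed path would fit equally well.** That holds in the two-variable case. A model with several latent variables and indirect paths may carry constraints that separate some directions, and the article shows no path diagram.
- **A group outside call-centres is needed.** H1 to H3 compare better and worse environments among call-agents, so it is not.

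**Conclusion.** The concern holds as a mismatch between the wording of H1 to H3 and the data described. All three can be tested only as associations at one time point; improvement and direction cannot be established. This rests on reading the design as single-wave, which everything in the article supports.

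For H1 and H3 there is a further limit. With no true association, a shared reporting tendency of 10% of variance already makes a significant result at n=500 more likely than not (0.61), and 20% makes it almost certain (0.995). These figures illustrate what the design cannot exclude; they are not estimates of what will happen. H1 also needs its outcome named for what it is, self-reported symptoms.

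No data collection has to change. The matter should be corrected because the hypotheses frame how the results will be read.

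**What to change.** 1. Restate H1 to H3 as cross-sectional associations: a better vocal-working environment is associated with better self-reported physiological voice symptoms (H1), better acoustic parameters (H2) and better psychosocial scores (H3).
2. Replace the causal and directional wording in Data analysis with a statement that these single-time-point data do not establish direction.
3. For H1 and H3, name common-method variance as a limitation and restrict the conclusions accordingly.

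The cost is a few sentences and a more modest conclusion.

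Refitting H1 and H3 with an exposure that the agent did not report, such as a centre mean or the manager interviews, may look like a cure, but the article does not provide for it. The interviews cover communication and training needs and are analysed thematically, and no centre identifier is described for the coded questionnaires. At the stated minimum of 10 centres, a centre-level correlation on 8 degrees of freedom must exceed 2.306/√(2.306² + 8) = 0.63 in size to reach p<0.05.

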Vilkman [5] states that the prevention and treatment of occupational voice disorders required improved OSH arrangements. Vocal strain was classified as 'repeated movements (and collisions) of the vocal folds' as a potential repetition strain injury (RSI). The occupational medicine definition of RSI is 'overload of repetitive movements and static and dynamic muscle loading combined with biomechanical, ergonomic and psychological factors as well as poor treatment of early symptoms' [6]. As vocal abnormality refers to the person's ability to cope with the working tasks, reliable and valid tools for reporting on voice complaints are important [5].

Call-centre workers have prolonged voice use and heavy vocal loading, thus increasing the risk of occupational dysphonia, which is a voice disorder due to work-related overuse or abuse that threatens communicative, interactive and economic efficiency [2,5,7,8]. Vocal loading may be attributed to prolonged voice use, and the work environment, where background levels of voice may affect the quality, type and loudness of phonation in speech. Jones et al [9] compared the prevalence of voice problems among telemarketers compared to the general population and concluded that they were twice as likely to report one or more symptoms of vocal strain compared with controls. In addition, impaired work productivity due to voice problems occurred in 31% of the telemarketers surveyed. Lehto [10] identified risk factors in voice professions as: background noise, poor air quality (dryness, dust), poor posture and vocal loading.

Risks to vocal performance and efficiency are not simply physiological, but in telephone interaction, also demand co-ordination of optimum psychological, behavioural and environmental settings to maintain an efficient balance for the interaction. Clearly, subtle paralinguistic vocal changes may unconsciously affect the call-agent, but also the receiver negatively. Cameron [11] describes the demands of this work environment as emotional, cognitive and vocal. Furthermore, the focus of training and quality monitoring has been vocal styling and not skilling for the task. Lehto [12] suggests that when the call-agent's voice becomes strained, hoarse or effortful, this in turn adds physiological and cognitive stress which can result in less efficient interaction, particularly when following a script or protocol for calls.

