## Methods and design

### Research design

This research will take the form of an occupational epidemiological study. This will be a mixed methods design, comprising a qualitative and large-scale quantitative approach, including acoustic measurement in the naturalistic work environment. There are three stages of this research study: 1. interviews with a senior manager (eg Call-centre or Human Resources Manager) within the call-centres; 2. online survey; and 3. acoustic measurements.

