### Research procedures

For the first stage of this research, interviews will be conducted with a senior manager (eg Call-centre or Human Resources Manager) within the call-centres. These interviews will aim to assess the organisation's communication and training needs and will be via telephone or face-to-face, whichever is the most convenient for the manager. Current occupational safety and health roles will be identified and the analysis of this information will further inform the measurement tool. Secondly, a large scale epidemiology study will be conducted consisting of an online biopsychosocial questionnaire, which will be administered to investigate the work environment and vocal demands of call-agents. This will be published on a secured website and accessed at a convenient time, in agreement with the management team in the call-centres. Participants will receive information on the study including the time required for completion and assurance that all responses are anonymous. The third and final stage will involve acoustic measurement from a monitored telephone call-sample of a random sample of participants, who participated in the online survey. A sample of the natural conversation will be selected by a call-centre staff member and given to the research team in digital format for analysis.

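### Noise on the work-call recordings can worsen several acoustic measures with no change in the voice, in the direction that favours hypothesis 2, and the stated plan does not separate the two

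*Protocol article*

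**What the plan says.** Under Data analysis, the protocol article states as its second hypothesis: "Call-agents' acoustic voice production is improved with good vocal-working environment". The acoustic results are to enter the structural equation model (SEM), which the same section describes as a confirmatory approach.

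The Background reports these risk factors from earlier work on voice professions: "background noise, poor air quality (dryness, dust), poor posture and vocal loading".

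Research design describes the study as "including acoustic measurement in the naturalistic work environment". Under Research procedures the signal is an "acoustic measurement from a monitored telephone call-sample of a random sample of participants, who participated in the online survey", and "A sample of the natural conversation will be selected by a call-centre staff member and given to the research team in digital format for analysis".

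Under Data analysis, three-second sections of the agent's "continuous voice uninterrupted by the customer will be selected during 10 seconds at the first, middle and the end of the call". Fourteen parameters are computed. They include mean, highest and lowest F0, the SD of F0, two jitter and two shimmer measures, and "Noise to Harmonic Ratio (NHR); Degree of Voice Breaks (DVB); Degree of Sub-harmonics (DSH); and Degree of Voiceless (DUV").

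Two arguments support the signal: the standing of the voice software as a reference tool, and the fact that three seconds lies within its manufacturer's range. SEM is said to deal with measurement error.

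**The concern.** If floor noise is part of the vocal-working environment, it can reach the acoustic outcome by two routes. One is through the agent's voice, which is what hypothesis 2 is about. The other is through the recording, because noise picked up on the call is analysed together with the voice. The second route makes a noisy floor look worse even when every voice is the same, so its sign agrees with hypothesis 2.

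A separate weakness concerns speech content. The extracts are unscripted, so some parameters depend on which sounds, pauses and intonation fall inside the cut.

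Neither stated argument for the signal addresses noise or content. Ordinary indicator error terms in an SEM assume error unrelated to the exposure, so they do not remove error that rises as the environment worsens. At stake is whether a positive result can be read as an effect of environment on the voice.

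**Working it through.** The plan gives no figure to reproduce here: it states that no power calculation was done, and it gives no noise level, effect size or SD. The one derived number is the minimum acoustic sample, 10% × 500 = 50 agents. With at least 10 centres that is about 50 / 10 = 5 per centre (Participants). Everything below is illustrative, with assumed inputs.

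**Step 1. Noise and a noise-to-harmonic measure.** If the autocorrelation peak is r = S/(S + N), then (1 − r)/r = N/S = 10^(−SNR/10). Assumed SNRs give:
- 25 dB: 0.003
- 20 dB: 0.010
- 15 dB: 0.032
- 10 dB: 0.100

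This is a generic index, not the software's own algorithm.

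**Step 2. One unchanged synthetic voice** (200 Hz, fixed jitter and shimmer, three seconds), with only the added noise varied. The telephone rows add a 300–3400 Hz band limit and 8-bit mu-law coding.

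| Condition | Index (1 − r)/r | Jitter % | Shimmer % | Mean F0, Hz |
|---|---|---|---|---|
| No noise | 0.003 | 0.31 | 1.5 | 200.0 |
| 20 dB | 0.013 | 0.38 | 4.0 | 200.0 |
| 10 dB | 0.103 | 0.75 | 9.5 | 200.0 |
| Telephone, no noise | 0.003 | 0.34 | 1.4 | 200.0 |
| Telephone, 20 dB | 0.010 | 0.40 | 3.9 | 200.0 |
| Telephone, 10 dB | 0.067 | 0.74 | 10.0 | 200.0 |

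The wideband values agree with step 1 plus the no-noise value: 0.010 + 0.003 = 0.013 and 0.100 + 0.003 = 0.103. From 20 to 10 dB the index rises by 0.103 − 0.013 = 0.090 wideband and by 0.067 − 0.010 = 0.057 over the telephone channel. Mean F0 does not move.

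**Step 3. Consequence for a test.** Take 50 agents in 10 centres of 5, an environment score set at centre level, and a true voice measure independent of it. Add an artefact that grows as the environment worsens. A Pearson test at two-sided 5% stands in for the SEM path. Share of significant results:

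| Artefact, SD per SD of environment | Significant |
|---|---|
| 0 | 4% |
| 0.25 | 37% |
| 0.5 | 84% |
| 0.75 | 98% |

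**Step 4. A channel effect unrelated to environment.** With the same layout and clustering ignored, the nominal 5% error becomes 8%, 9%, 14% and 24% at assumed between-centre ICCs of 0.05, 0.10, 0.20 and 0.40. This is extra error and clustering, with no preferred direction.

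**Step 5. Speech content.** Taking the degree of voiceless, as its name indicates, to be 100 × the unvoiced share of the extract, shares of 0.10, 0.30 and 0.50 give 10, 30 and 50 from the same voice. Voice breaks respond likewise to pauses, and the SD, highest and lowest F0 respond to the intonation of the phrase that was cut.

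**The case against.** Several points on the other side stand.

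- **Exposure not defined.** The article never sets out what makes up a good vocal-working environment, and the questionnaire is still to be developed. That noise belongs to it is a reasonable inference from the Background, not a stated definition.
- **Design choice.** Recording real calls at work is deliberate. A journal article may leave recording specifications to a fuller protocol, so their absence is not the point. The point rests on what the article does fix: source, setting, speech material, parameters and hypothesis.
- **Real responses to noise.** The Background says that background voice levels may alter how agents phonate, including loudness. Agents who speak up lose less SNR than the floor noise alone implies, and a worse value in noise may be a true voice change. The planned recordings cannot tell these apart.
- **Exploratory wording.** The article also says relationships will be explored and that findings will feed a later trial's power calculation. That softens the matter, but the same section calls the SEM hypothesis-testing.

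A reader might infer more than the documents support:

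- That noise, telephone system and speech content all push towards hypothesis 2. Only noise has a known direction. The other two bias the result only if they vary with environment.
- That all fourteen parameters are affected by every route. Mean F0 was insensitive to noise in step 2.
- That headsets and recording systems differ between centres. This is plausible, but no section describes them.
- That 0.09 is the expected shift. It rests on assumed SNRs and a generic index, and the telephone channel gave 0.057.
- That noisy recordings must be excluded, or centre fixed effects imposed. With about five agents per centre, either could remove much of the environmental contrast under test.

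**Conclusion.** The point holds in a limited form. For the noise-to-harmonic ratio, shimmer and jitter, noise on the recording can mimic a worse voice in the direction of hypothesis 2, and nothing stated in the article separates that from a real effect. Voiceless degree, voice breaks, and the SD, highest and lowest F0 are weak indicators of dysphonia in unscripted three-second cuts. Telephone-system and content differences otherwise add error and within-centre clustering.

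The size of the bias cannot be computed from the documents. The simulations show only that, with 50 agents, a moderate artefact would be enough to produce frequent false support. They rest on assumed noise levels, artefact sizes and ICCs, and on a simple correlation in place of the SEM. A positive finding would not be worthless, but in the noise-sensitive measures alone it would not show that environment changes the voice.

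**What to change.** In the acoustic part of Data analysis:

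1. Report the degree of voiceless, degree of voice breaks, highest and lowest F0 and the SD of F0 descriptively. Keep them out of the acoustic indicators of the dysphonia model.
2. Estimate the noise level or SNR of each recording from the call file, where it contains a stretch in which neither party speaks. Record the centre and its recording system.
3. Repeat the hypothesis 2 analysis with adjustment for SNR, and again with a centre term. Make these sensitivity analyses, not mandatory exclusions or fixed effects, and note that each may also remove part of a real environmental effect.
4. State in advance that an association seen only in noise-sensitive measures, or one that disappears in these analyses, will be reported as exploratory and not as evidence that environment changes the voice.

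This needs only the planned recordings and a short computation on each, plus a note of centre and system. The cost is five fewer acoustic indicators in the model and a more cautious conclusion on hypothesis 2. Some files may have no usable silent stretch, so the SNR analysis may cover only part of the sample.
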